#### Food Groups and Misreporting

Foods and beverages consumed during the controlled feeding sessions will be matched to the food codes from Australian food composition tables (AUSNUT 2011-2013) using a nutrition analysis software (FoodWorks 10, Xyris Software). The measured quantities of the foods and drinks consumed in the food laboratory will be coded. The observed intake of the provided food groups will be calculated. In ASA24, Intake24, and mFR24 data sets, foods and drinks that were reportedly consumed outside of the food laboratory (eg, snacks) will be removed before analysis based on the reported eating occasions and time.

The 24HR data on food and beverage intake from each method will be compared with the observed weight and daily intake of food and beverages to identify 4 types of misreporting, that is, omissions, intrusions, misclassifications, and portion misestimations. The following 5 steps will be used:

Matches between reported and observed intake will be identified by comparing the assigned food codes. Food codes correspond to a food grouping hierarchy in which the first 2 digits indicate the major food groups (eg, dairy, meat, and vegetables), the first 3 digits indicate the submajor food groups (eg, milk products and dishes), and the first 5 digits indicate the minor food groups (eg, dairy milk, yogurt, and cheese) [77]. Food codes of reported and observed intake data will be considered an exact match if they belong to the same minor food group. Foods codes from the same submajor food group will be considered a close match, whereas foods from the same major food group will be considered a far match.Omissions, which are items that were consumed but are not reported, will be identified, and omission rates at each food group level will be calculated using the formula:sum of omissions / (sum of omissions + sum of all matches) × 100%.Omission rates of mixed meals, single items, and condiments will be calculated. Differences in omission rates by 24HR method will be assessed using chi-square tests.The proportion of misclassifications, which are incorrect descriptions of consumed items, will be defined as close or far matches. Differences in the proportion of misclassifications within food groups by the 24HR method will be assessed using chi-square tests.Intrusions, which are items that are reported but were not consumed, will be identified, counted by food group, and expressed in kilojoules.Misestimation of portion size will be assessed by comparing the intake of food item matches in grams for each 24HR method with observed intake using a paired samples statistical test.

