## Methods

### Sample and Recruitment

The sample will be selected from adults aged 18-70 years residing in Perth, the capital city of Western Australia, Australia, and recruited via the electoral roll by selecting postcodes that provide representation across socioeconomic status. Other recruitment methods will include advertising on the Curtin University website and a snowball methodology (eg, email newsletter and referrals from friends or colleagues). A final sample of 150 randomized participants (allowing for a 20% dropout) will allow for 90% power at a 5% significance level when the true difference between any 2 mean differences between estimated and observed dietary energy intake is 0. Quota sampling will be used to ensure that equal numbers of men and women are recruited. To be included in the study, participants must be able to attend in-person feeding sessions on 3 separate days and have access to a computer and a smartphone (running iPhone operating system or Android operating system) with a data plan. Exclusion criteria include serious illnesses or medical conditions, pregnancy, special dietary requirements, or dietary restrictions because of food allergies or intolerances or dieting to lose weight.

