### Study Design

A controlled feeding study with a crossover design will compare the accuracy of 3 technology-assisted methods of assessing 1 day of dietary intake: ASA24, Intake24, and mFR24. The sequence of the 3 dietary assessment periods will be randomized for each participant, with a 1-week washout period between each feeding session (Figure 1). Therefore, each participant will be exposed to each of the 3 methods at different periods. The crossover design, a repeated measurement design, will allow both between-group and within-group method comparisons. This design yields a more efficient comparison of treatments than a parallel design because fewer participants are required in the crossover design to attain the same level of statistical power or precision as a parallel design.

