### Data Analyses

#### Energy Intake Estimation Accuracy

The participant feeding days with at least two meals eaten at the food laboratory will be included in the analyses. Daily energy intake from each 24HR method and the controlled feeding sessions will be calculated, excluding any items reportedly consumed outside of the food laboratory. Outlier checks will be conducted to identify any obvious keying errors or food composition data anomalies, which will be corrected before proceeding. Bland-Altman plots will be used to test for agreement between the 24HR values and controlled feeding measures at the individual and group levels. Repeated measurements will be analyzed using the linear mixed models procedure using SPSS version 25, accounting for age, gender, and BMI, with 24HR method and method order as fixed effects, to assess whether there are statistically significant differences by 24HR method. Misreporting will be assessed by examining the ratio of reported 24HR intake to observed intake, with the lowest tertile considered to indicate underreporting. The proportion of underreporters in each 24HR method will be compared using chi-square tests and logistic regression. Among underreporters, the total energy misestimation will also be compared using regression models adjusted for age, gender, and BMI.

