#### Correlates of Energy Misestimation

Psychosocial, demographic, and cognitive factors associated with omission and intrusion rates and with energy misestimation on each 24HR method will be evaluated using chi-square tests and multivariate logistic regression. The effects of factors will be reported as odds ratios and associated 95% CIs. Some dietary factors in the Accuracy and Cost-effectiveness of Technology-Assisted Dietary Assessment study are standardized because of the controlled feeding methodology (meal frequency and eating location), but it is hypothesized that food and meal complexity and physical form will affect reporting accuracy via an interaction with cognitive factors. P<.05 will be considered statistically significant in all analyses.

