#### Acceptability

Differences in acceptability among methods indicated by the rating and proportions of participants agreeing with each of the ease-of-use statements will be assessed using chi-square tests. Demographic correlates of a preference for a particular method will be explored using multivariable logistic regression, adjusting for method order.

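### Chi-square tests between methods ignore that the same participants supply all three recalls, and food-level tests ignore that foods cluster within a recall

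*Protocol article*

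**What the plan says.** Study Design sets out a crossover in which "each participant will be exposed to each of the 3 methods at different periods". The Data Analyses sections then name these tests:

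- **Underreporting** (Energy Intake Estimation Accuracy): "The proportion of underreporters in each 24HR method will be compared using chi-square tests and logistic regression". No within-person term is mentioned for the logistic regression.
- **Omissions** (Food Groups and Misreporting): "Differences in omission rates by 24HR method will be assessed using chi-square tests". The rate is the number of omitted items divided by omitted plus matched items, so the single food is the unit.
- **Misclassification** (same section): also chi-square, within food groups. The Abstract extends chi-square to intrusion rates.
- **Portion size** (same section): a comparison of "food item matches in grams for each 24HR method with observed intake using a paired samples statistical test".
- **Acceptability**: the "proportions of participants agreeing with each of the ease-of-use statements will be assessed using chi-square tests".

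The threshold is common to all of them: "P<.05 will be considered statistically significant in all analyses".

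Other parts of the plan do respect the repeated measurements. Energy intake is analysed with a linear mixed model that has method and method order as fixed effects, and time and total costs with repeated measures analysis of variance.

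**The concern.** A Pearson chi-square test treats every count as coming from an independent unit. Two features of this trial break that assumption, and they act in different directions.

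First, the three proportions being compared come from the same people. Someone who underreports with one tool is likely to underreport with another, and the test does not credit this pairing. Strengths and Limitations presents the within-person comparison as an important advantage of the study; for underreporting and acceptability the named test gives that advantage away.

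Second, omissions, misclassifications and portion errors are counted per food, and one recall contributes several foods. If recall quality varies from one day to the next, the foods of one recall go wrong together, and counting them as independent overstates the information.

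At stake is whether the p values for several outcomes under the first objective, which covers accuracy and acceptability, mean what they say.

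**Working it through.** **Inputs from the article.** Three methods per participant, and a 5% threshold. Sample and Recruitment states: "A final sample of 150 randomized participants (allowing for a 20% dropout) will allow for 90% power at a 5% significance level". Taking 20% off gives 150 × 0.8 = 120 completers. The article states no power or error rate for the analyses considered here, so there is no figure of its own to reproduce. Its power statement concerns energy intake, gives no standard deviation or margin, and does not bear on this point.

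**Inputs assumed.** Foods per recall (m), all correlations, and an omission rate of 15% or 20% in the simulations. An underreporting rate of one third follows if the tertile is cut over all recalls together.

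**1. Person-level proportions.** With one yes/no result per person and method and within-person correlation ρ, the three-method Pearson statistic under no difference behaves like (1 − ρ) times a chi-square on 2 degrees of freedom. For 2 degrees of freedom the tail probability is exp(−x/2) and the critical value is 5.99, so

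actual size = exp(−5.99 / [2(1 − ρ)]) = 0.05^(1/(1 − ρ)).

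| ρ (assumed) | Actual size | Chi-square p when the correct p is 0.05 |
|---|---|---|
| 0.1 | 3.6% | 0.067 |
| 0.3 | 1.4% | 0.123 |
| 0.5 | 0.25% | 0.224 |

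The last column is 0.05^(1 − ρ). Simulation with 120 people and a rate of one third agrees: the size of the chi-square test is 3.3%, 1.3% and 0.3% at correlations of 0.12, 0.32 and 0.48, while Cochran's Q stays at 5.0% to 5.1%. As an illustration of lost power, with assumed rates of 25%, 33% and 42% and a correlation of about 0.31, chi-square has about 73% power and Cochran's Q about 88%. The gap narrows as the correlation falls.

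**2. Food-level rates.** Let ρw be the correlation between foods in the same recall and ρb that between foods in different recalls of the same person. The variance factor is

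D = 1 + (m − 1)ρw − mρb, and actual size = 0.05^(1/D).

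With ρw = 0.10:

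| Foods per recall | ρb = 0 | ρb = 0.05 | ρb = 0.08 | ρb = 0.10 |
|---|---|---|---|---|
| 2 | D 1.10, 6.6% | D 1.00, 5.0% | D 0.94, 4.1% | D 0.90, 3.6% |
| 15 | D 2.40, 28.7% | D 1.65, 16.3% | D 1.20, 8.2% | D 0.90, 3.6% |

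The test is anticonservative only if ρw exceeds ρb × m/(m − 1). A stable person effect makes the two correlations equal and pushes the size below 5%.

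Simulations with 120 people agree:

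- At 15 foods, 20% omissions and ρw about 0.105, the size is 17%, 25% and 29% for ρb of 0.051, 0.025 and 0, and 3.1% for ρb = ρw. An analysis of per-person rates stays between 4.3% and 5.5%.
- A logistic model with person standard deviation 0.5, person-day standard deviation 0.5 to 0.8 and 15% baseline omission gives 13% to 25% at 15 foods, 7% to 10% at five, 5% to 7% at three and 5% to 6% at two.

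**3. Portion size.** This test compares one method with observed intake, so only clustering within the recall matters. If single foods are the unit, D = 1 + (m − 1) × ICC and the size is 2Φ(−1.96/√D).

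- m = 15: ICC 0.05 gives D 1.7 and 13%; ICC 0.10 gives D 2.4 and 21%; ICC 0.20 gives D 3.8 and 32%.
- m = 2: 5.6% to 7.4% over the same ICC range.

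**The case against.** Four points on the other side deserve weight.

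**The crossover is not dropped throughout.** A reader might infer that the plan respects repeated measurement only for energy. It does not follow: costs are compared by repeated measures analysis of variance, and the model for the preferred method adjusts for method order. This objection stands, and the point is confined to the outcomes listed above.

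**Food-level p values need not be far too small.** That reading is tempting, but it needs many foods pooled in one test and correlation specific to the recall. The article calculates omission rates by food group and compares misclassification within food groups, where a recall may contribute only two or three foods and the error is near 5%. It gives neither food counts nor correlations. This also stands: the error rate is uncontrolled rather than known to be high. Recall-specific correlation is plausible, because each method has its own feeding day and its own recall.

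**A between-method analysis of portion size may be planned.** Food Groups and Misreporting compares each method only with observed intake, so one might conclude that methods are never compared on portion error. The Abstract, however, lists portion sizes among the estimates and then names linear mixed models for differences between methods. The supported point is that the two places should be aligned. Nor does the article say whether the paired test uses single foods or per-person means, so the inflation in step 3 is conditional.

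**"Chi-square" might loosely cover McNemar or Cochran's Q, with details left to an analysis plan.** The article does not say so, and those tests would not fit pooled food counts, because different foods are eaten on each day. Since it names the test, the matter is not simply left open.

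Finally, the person-level error is conservative: it costs power and does not create false findings.

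**Conclusion.** The point holds in limited form and should be fixed. For underreporting and acceptability the named test is mismatched to the design, and its p values are too large for any positive within-person correlation; only the amount (actual size 3.6% down to 0.25%) depends on the assumed correlation of 0.1 to 0.5.

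For omissions and misclassification the direction cannot be known in advance. The size runs from about 3%, through near 5% for small food groups, to roughly 13% to 29% for about 15 pooled foods when much of the correlation belongs to the recall; a smaller recall-specific share gives less, such as the 8% in the table. For portion size the test is anticonservative if it is run on single foods and those foods are positively correlated within a recall.

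The main energy comparison and the cost comparison use methods that allow for repeated measurements, so this point does not touch them.

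**What to change.** - **Underreporting and acceptability:** replace chi-square by Cochran's Q with McNemar tests for pairs, or by GEE or mixed logistic models clustered on participant, with method and order as fixed effects. The models also settle what the logistic regression for underreporters should contain.
- **Omissions and misclassification:** use models with participant and participant-by-day (recall) effects, or compute a rate per person and method and compare those within person. The Abstract's statement on intrusion rates should follow the same approach.
- **Portion size:** state the unit. Use the mean error per person, or a mixed model with method as a fixed effect, and bring Food Groups and Misreporting into line with the Abstract on the comparison between methods.

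None of these requires a correlation to be assumed beforehand. The cost is a change to the analysis wording and modest extra programming; no new data are needed.

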**Methods:**

Using a controlled feeding study design, 24HR data collected using 3 methods will be obtained for comparison with observed intake. A total of 150 healthy adults, aged 18 to 70 years, will be recruited and will complete web-based demographic and psychosocial questionnaires and cognitive tests. Participants will attend a university study center on 3 separate days to consume breakfast, lunch, and dinner, with unobtrusive documentation of the foods and beverages consumed and their amounts. Following each feeding day, participants will complete a 24HR process using 1 of 3 methods: the Automated Self-Administered Dietary Assessment Tool, Intake24, or the Image-Assisted mobile Food Record 24-Hour Recall. The sequence of the 3 methods will be randomized, with each participant exposed to each method approximately 1 week apart. Acceptability and the preferred 24HR method will be assessed using a questionnaire. Estimates of energy, nutrient, and food group intake and portion sizes from each 24HR method will be compared with the observed intake for each day. Linear mixed models will be used, with 24HR method and method order as fixed effects, to assess differences in the 24HR methods. Reporting bias will be assessed by examining the ratios of reported 24HR intake to observed intake. Food and beverage omission and intrusion rates will be calculated, and differences by 24HR method will be assessed using chi-square tests. Psychosocial, demographic, and cognitive factors associated with energy misestimation will be evaluated using chi-square tests and multivariable logistic regression. The financial costs, time costs, and cost-effectiveness of each 24HR method will be assessed and compared using repeated measures analysis of variance tests.

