### Objectives

This research protocol will compare 3 leading technology-assisted dietary assessment methods. Using a controlled feeding study design with healthy adults aged 18 to 70 years, this study will (1) compare the accuracy, acceptability, and cost-effectiveness of 3 technology-assisted 24HR methods (ASA24, Intake24, and mFR24) relative to observed intake for 3 meals on 1 day; (2) test the accuracy of automated methods for determining food and beverage intake using food images and image analysis, computer vision, and machine learning techniques; and (3) assess associations between reporting errors and demographic, psychosocial, and cognitive factors.

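### For portion size, the Methods specify only tests of each recall method against observed intake and no test between methods, and the abstract does not clearly agree

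*Protocol article*

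**What the plan says.** The Objectives section sets out to "compare the accuracy, acceptability, and cost-effectiveness of 3 technology-assisted 24HR methods" relative to observed intake. The Food Groups and Misreporting section names portion misestimation as one of four error types and handles the four in five steps.

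- Omissions: "Differences in omission rates by 24HR method will be assessed using chi-square tests".
- Misclassifications: "Differences in the proportion of misclassifications within food groups by the 24HR method will be assessed using chi-square tests".
- Portion size: assessed by "comparing the intake of food item matches in grams for each 24HR method with observed intake using a paired samples statistical test". No comparison across methods is named in this step.

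In the Methods, the mixed model with method as a fixed effect appears only under Energy Intake Estimation Accuracy, where it is used "to assess whether there are statistically significant differences by 24HR method".

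The abstract is broader. It says: "Estimates of energy, nutrient, and food group intake and portion sizes from each 24HR method will be compared with the observed intake for each day". Its next sentence is "Linear mixed models will be used, with 24HR method and method order as fixed effects, to assess differences in the 24HR methods", and that sentence is not restricted to energy.

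The threshold is common to everything: "P<.05 will be considered statistically significant in all analyses".

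**The concern.** Two null hypotheses are involved. The paired test has the null that mean portion error is zero for one method. The objective needs the null that portion error is equal across the three methods. Three separate tests of the first kind do not add up to a test of the second. If one method is significant and another is not, that is not evidence that they differ.

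The gap works in both directions. At low or moderate power, methods with the same error can fall on different sides of .05. A noisier method is also less likely to be flagged, so it can look better than a more consistent one with the same mean error. At very high power, all three tests can be significant although one method's error is much larger, and the tests say nothing about that difference.

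Portion misestimation is one of the error types the study is built to examine. Each participant uses all three methods, so a within-person contrast is available from data already being collected.

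**Working it through.** **Inputs from the protocol.** 150 randomized with 20% dropout (Sample and Recruitment), so 150 × 0.8 = 120 completers. Significance level 0.05, taken here as two-sided. The 90% power statement concerns energy intake only. No SD, bias, correlation or power is given for portion size, so there is no plan figure to reproduce on this point.

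**Assumptions.** One portion error per participant per method, n = 120, the same true mean error in all three methods, and error expressed in SD units. Within-person correlation between methods is varied from 0 to 0.7.

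**Step 1: independent errors.** Let p be the power of each paired test. The three verdicts disagree (one or two of three significant) with probability 1 − p³ − (1 − p)³.

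| Power of each test | Mixed verdicts |
|---|---|
| 5% (no true error) | 14% |
| 20% | 48% |
| 50% | 1 − 0.125 − 0.125 = 75% |
| 80% | 48% |
| 90% | 1 − 0.729 − 0.001 = 27% |
| 95% | 14% |
| 99% | 3% |

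**Step 2: correlated errors.** The three test statistics were simulated 400,000 times per setting at n = 120. A common error of (1.960 + 1.282)/√120 = 0.296 SD gives each test 90% power, and 0.18 SD gives about 50%.

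| Common error | Correlation 0 | 0.3 | 0.5 | 0.7 |
|---|---|---|---|---|
| 0 | 14.2% | 13.5% | 12.2% | 10.1% |
| 0.18 SD | 75.0% | 60.5% | 50.0% | 38.0% |
| 0.296 SD | 26.9% | 23.4% | 20.3% | 15.9% |
| 0.40 SD | 2.3% | 2.2% | 2.0% | 1.7% |

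**Step 3: same mean error, different spread.** With a common mean error of 0.2, error SDs of 0.8, 1.0 and 1.4, and correlation 0.3, the three tests have power of 78%, 59% and 35%. Verdicts are mixed in 67% of trials. The noisiest method is the least often flagged.

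**Step 4: high power, real difference.** Simulated power is 99.2% at 0.4 SD and rounds to 100% at 0.5 SD. Suppose two methods have an error of 0.4 SD and the third 0.8 SD. All three tests are then significant in at least 1 − 0.008 − 0.008 − 0.000 = 98.4% of trials, although one error is twice the others.

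**Step 5: one between-method test.** In the Step 2 simulation, a single 2-df test of equal error across methods declared a difference in 4.9% to 5.1% of trials, whatever the common error or correlation.

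**The case against.** A reader of the Methods might infer that portion size is never compared between methods. The abstract does not support that. It lists portion sizes and follows at once with an unrestricted mixed model for method differences. The abstract also carries a between-method test for intrusions that the intrusion step in the Methods omits, so silence in one step does not prove that no test is planned. This stands, and it limits the point to what the Methods specify and to the disagreement with the abstract.

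A reader might also infer that equal methods will often get different verdicts. That is conditional. The high figures come from intermediate power and low correlation. Step 5 of the plan works on food-item matches over up to three meals, and pooling many items could push power to where mixed verdicts are rare. The percentages should not be set against 5% as if they were a false-positive rate: with zero error, three independent tests disagree 14% of the time by construction, and where every method is biased each rejection is correct. Only the inference of a difference is unsupported.

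Nor does the protocol say that methods will be ranked by significance, or that a non-significant result means accurate portions. The mean gram errors would let a reader see a large difference, though without an interval or test for it.

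Testing each method against observed intake is a legitimate question, and a condensed article may leave detail to an analysis plan. But here the article does state a specific test for portion size. That test answers a different question from Objective 1, while the omission and misclassification steps beside it name between-method tests.

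**Conclusion.** The point holds in limited form. The only test that the Methods assign specifically to portion size does not compare methods, and the abstract leaves open whether the mixed model covers it.

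The size is conditional on assumed inputs. With independent errors, mixed verdicts for identical methods run from about 14% to 75% at per-test power of 5% to 95%, and are about 3% at 99%. At correlation 0.7 they are 38% at about 50% power and 16% at 90%. At the high-power end the separate tests instead fail to show real differences. The SD units, the correlations and the one-error-per-participant structure are all assumptions, and no rate can be claimed for this trial. The case for change rests on the mismatch between the null tested and the objective, which does not depend on those inputs.

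This is worth correcting, but it concerns one component of the accuracy comparison and leaves the energy analysis untouched.

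**What to change.** State in the portion-size step that a mixed model of the type planned for energy will be fitted to matched-item portion error (reported minus observed grams). Method and order would be fixed effects, and participant and food item random effects, since one person contributes several matched items. Report the pairwise method differences with 95% CIs.

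Each method's mean error against observed intake can be kept alongside with its CI. Add that differences between methods will not be inferred from which separate test is significant. Word the abstract and the Methods so that both say the same about which outcomes the mixed model covers.

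The cost is about one sentence of analysis text. It needs no new data, and the model type is already planned.
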